### Sample size {14}

Approximately 1000 children will be screened every day. Based on previous programmes, we expect approximately 160 of these children to be identified as requiring referral for further assessment and treatment. All of these children’s parents/guardians would receive the standard SMS reminders in a standard programme.

The adaptive allocation method that we are using does not use a pre-specified a sample size. Instead, the study will run until one of two criteria is met:There is a >95% probability that one arm is best.There is a >95% probability that the difference between the arms remaining in the study is <1%.

Depending on the effect of the interventions, one of the stopping criteria might be met after a few days; however, it could also take years before reaching a definitive conclusion. We will set a 3-month limit for this current study due to resource constraints.

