### Objectives {7}

Our objectives are to test a behavioural economics-informed SMS reminder message and a pre-recorded voice message that will be sent to the parents/guardians of school children who have been identified as having a visual impairment and referred to clinic. We hypothesise that these messages will be associated with a higher attendance rate than the current standard SMS reminder that is sent to all referred patients’ parents/guardians.

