**Fig. 1 Fig1:**
[figure not shown]
First draft SMS reminder. Note: ‘Tebogo’ and ‘[name] are not real names

We will use four arms as outlined below. Each SMS will be sent two times; on the day of referral and on the day before the appointment.

Initially, we will only test arms 1 and 2 (the control and intervention SMS messages). We plan to introduce the voice message arms after 6 weeks. This is because we are interested in introducing new arms at later stages in the screening programme and want to observe how the allocation algorithm handles the introduction of new arms part-way through testing established interventions.Arm 1 (Control): Standard SMS reminder messages.Arm 2: New SMS reminder messages.Arm 3: Standard SMS reminder messages plus the pre-recorded voice reminderArm 4: New SMS reminder messages plus the pre-recorded voice reminder

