### Outcomes {12}

All children who are screened and found to need further assessment and treatment (e.g. refractive services) will be given an appointment, approximately 1 week later, at a specified field ‘triage and treatment’ clinic or at a specialist ophthalmic hospital clinic. The primary outcome is attendance at this pre-specified appointment on the appointment date (yes/no).

The Peek software retains a record of every referred child. When children attend for these appointments, they are checked in using Peek software. This automatically updates their attendance status. Attendance data will be automatically reviewed by an algorithm every 24 h. The great advantage of the Peek-based screening programme is that is a closed data system with complete, unified data records for every person screened, their referral status and their attendance status. No additional data collection activities are required.*Primary outcome*: attendance at clinic on invited date. This is a binary outcome measure (yes/no). We will compare mean outcome rates between arms.*Secondary outcome*: days elapsed between appointment date and attendance. This is because children may miss their appointed day but attend at a later date. We will compare mean number of days elapsed between each arm.*Subgroup analyses*: attendance by age, sex, urban/rural residence, distance to clinic, ethnicity, guardianship, religion, language, household composition, migrant status, parental occupation, housing, assets and income.

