### Statistical methods

#### Statistical methods for primary and secondary outcomes {20a}

This study will use Thompson sampling a Bayesian approach to identify the best arm. This is a Bayesian algorithm widely used to learn about arms and optimise decision making [27] Every 24 h, the probability of each arm being the best arm overall will be estimated, using Monte-Carlo simulations to get the posterior probability estimates. As there is no evidence available on how the messages would perform relative to another, a regularising prior of Beta(100,000) (i.e. centred at *p*=0.5 with a 90% credible interval of 0.44–0.56) will be used to avoid overfitting extreme data in the early phase of the trial. It is expected that about 1,000 children will enrol every day, and the observed data will begin to dominate the prior within the first couple of days. Each arm will have a probability of being best between 0 and 100%, and the sum of all two probabilities will equal 100%. These probabilities will be compared to the stopping rules as to whether the trial should stop or continue into the next day. If the trial is to continue, the proportion allocated to each arm for the next day will be updated to be proportional to the estimated probabilities. We will conduct all analyses using the runif and rbeta functions in R (R Foundation for Statistical Computing, Vienna, Austria). Figure 2 illustrates participant flow and operation of the algorithm.

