#### Interim analyses {21b}

This is an automated adaptive trial. Our algorithm will review the attendance data every 24 h and perform statistical testing. Two stopping rules will be applied during these daily interim analyses:There is a >95% probability that one arm is best.There is a >95% probability that the difference between the arms remaining in the study is <1%.

If neither of these rules have been satisfied, then the trial (i.e. enrolment) will continue until three months of active screening have elapsed. The Bayesian algorithm will adjust the allocation ratio based on the performance of each arm with respect to the updated posterior probability that each is associated with attendance (Fig. 3).

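### The stopping rules are not suspended during the two-arm stage, so the trial can end before the voice arms open at six weeks

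*Protocol article*

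**What the plan says.** Objectives {7} sets out to "test a behavioural economics-informed SMS reminder message and a pre-recorded voice message", and Trial design {8} calls the trial four-arm. Under Intervention description {11a}, only the control SMS and the new SMS run at first: "We plan to introduce the voice message arms after 6 weeks". Participant timeline {13} repeats the staged entry.

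On stopping, Interim analyses {21b} says: "Two stopping rules will be applied during these daily interim analyses". The first is "There is a >95% probability that one arm is best". The second is "There is a >95% probability that the difference between the arms remaining in the study is <1" (per cent). Outcomes {12} confirms the frequency: "Attendance data will be automatically reviewed by an algorithm every 24 h". Sample size {14} makes meeting either rule the end of the study, subject to a three-month cap, and adds that "Depending on the effect of the interventions, one of the stopping criteria might be met after a few days".

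On allocation, Statistical methods {20a} gives one regularising prior, centred at 0.5 with a 90% interval of 0.44 to 0.56, and then says that "the proportion allocated to each arm for the next day will be updated to be proportional to the estimated probabilities". It gives no minimum share, and it speaks of two probabilities summing to 100%, which describes the two-arm stage.

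**The concern.** Two parts of the plan run on separate clocks. The stopping clock starts with the first outcomes, in about the second week. The voice clock starts at week six. No section says that the first waits for the second, and none sets a burn-in or a minimum sample. If a rule is met while only the two SMS arms are open, the study as written is over, and arms 3 and 4 never recruit.

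The design then works against its own objective: the better the new SMS performs, the less likely it is that voice is ever tested. Early stopping also defeats the reason given for staged entry, which is to watch the algorithm absorb new arms.

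A second issue arises only if week six is reached. Allocation follows the probability of being best, and on the first day of the voice arms that probability depends on the prior they are given, because they have no data.

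**Working it through.** **Inputs from the protocol.** Referrals: about 160 a day (Sample size {14}). Attendance: around 50% (Background {6a}). Outcome lag: about one week (Outcomes {12}). Both rules and the daily looks: {21b}. Allocation: 1:1 at first, then proportional to P(best) ({8}, {20a}). Voice entry: six weeks ({11a}).

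**Assumptions.** Six weeks = 30 working days, one week = 5 working days, three months = 65 working days. No effect size is stated, so gains of 0 to 10 percentage points are used.

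**Prior.** Beta(100,100) has a 90% interval of 0.442 to 0.558, which reproduces the stated 0.44 to 0.56. The printed Beta(100,000) does not match that interval and may be a typesetting slip. Beta(100,100) is used throughout.

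**Step 1: what one look at day 30 would give.** Matured outcomes: (30 − 5) × 160 = 4,000, or 2,000 per arm at 1:1. P(arm 2 best) is approximately Φ(z), with z = (m2 − m1)/√(v1 + v2), and rule 1 needs |z| > 1.645. The posterior SD of the difference is √(2 × 0.25/2,201) = 0.0151.

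- At +2 points: m2 = (100 + 1,040)/2,200 = 0.518, so expected z = 0.0182/0.0151 = 1.21.
- At +5 points: m2 = (100 + 1,100)/2,200 = 0.545, so expected z = 0.0455/0.0151 = 3.02.

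Across repeated trials, z varies with SD [√(2 × 0.25/2,000) × 2,000/2,200]/0.0151 = 0.95. A single look would therefore meet rule 1 in about 8% of trials at no difference, 32% at +2 and 92% at +5.

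**Step 2: daily looks.** The two-arm stage was simulated with the lag, the daily reallocation and the rules at every look (4,000 runs per row, normal approximation to the Beta posteriors). Chance of stopping before voice opens:

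| True SMS gain | 160/day, 50% base | 160/day, 60% base | 42 days, 7-day lag, 50% base | 1,000/day, 50% base |
|---|---|---|---|---|
| 0 | 25% | 36% | 30% | 41% |
| +1 | 34% | 46% | 40% | 66% |
| +2 | 51% | 62% | 59% | 95% |
| +3 | 69% | 80% | 81% | 99.9% |
| +5 | 94% | 98% | 99% | 100% |
| +10 | 100% | 100% | 100% | 100% |

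In the first column the median stopping day is about 12 at +5 and 9 at +10. All stops came from rule 1; rule 2 never fired. The last column uses the enrolment figure in {20a}, which differs from the 160 referrals in {14}.

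**Step 3: voice share at entry, if the late arms start on the same prior.** This is an inference, because {20a} does not address late arms. With 2,000 matured outcomes per SMS arm, the combined voice share on the first day is:

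| Both SMS arms at | Voice share |
|---|---|
| 40% | about 100% |
| 50% | 67% |
| 55% | 15% |
| 60% | under 1% |
| 65% | about 0% |

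Hand check at 60%: SMS posterior mean 1,300/2,200 = 0.591, SD √(0.591 × 0.409/2,201) = 0.0105; voice prior SD √(0.25/201) = 0.0353. The chance that one voice arm beats one SMS arm is Φ(−0.091/√(0.0105² + 0.0353²)) = Φ(−2.47), about 0.7%. This agrees with the table.

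**The case against.** The strongest reply is that early stopping is disclosed. Sample size {14} says openly that a rule could be met in days or could take years, and the protocol commits to no effect size. That stands as far as it goes: with no SMS difference, or a 1-point one, most trials at 160 a day do reach the voice stage. A reader might infer that the trial will usually stop early. The documents do not support that, since it needs a gain of roughly 2 to 3 points that the protocol never states. But admitting that a rule may fire early does not say what then happens to the two arms not yet opened, and under identical messages about one trial in four still ends without them.

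A second reply is that how added arms are initialised is commonly left to an analysis plan, and the algorithm and allocation figures are not shown. This also stands, and it limits the starvation point. A reader might infer that the voice arms will be starved. At the protocol's own 50% attendance the opposite holds: they would take about two thirds of allocation at entry. Starvation needs both SMS arms, including the unchanged standard message, near 60% or more.

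The same reply does not rescue the stopping rules. The article itself fixes the rules, their daily timing, the consequence of meeting one and the voice entry date, and these stated parts do not fit together.

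**Conclusion.** The stopping rules and the six-week voice entry are unreconciled. As written, rule 1 can end the trial in its two-arm stage, with probability about 25% at no SMS difference, 34% at +1 point, 51% at +2, 69% at +3, 94% at +5 and 100% at +10. These figures rest on 160 referrals a day, 50% base attendance, a 5-working-day lag and Beta(100,100). A higher base, calendar days or the higher enrolment figure all raise them.

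The allocation point is secondary and conditional on late arms sharing the 0.5-centred prior. If they do, early voice exposure reflects the distance of attendance from 0.5 and not the merit of the message, in either direction.

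**What to change.** In {14} and {21b}, state that neither stopping rule is evaluated until the voice arms have opened, have completed a fixed equal-allocation run-in (for example 10 working days), and those outcomes have matured. In {20a}, state that allocation is equal across the four arms during that run-in, so that data and not the prior set voice exposure afterwards. The run-in alone gives the voice arms 10 × 160 × 2/4 = 800 children.

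An illustrative simulation (200 runs per scenario, all data retained) supports both parts. With true attendance of 50/55/55/60% in arms 1 to 4, arm 4 is declared best by day 65 in 88% of runs, against 2% as written. With 60/62/65/67% the figures are 62% against 0%. Suspending the rules only until voice opens, without the run-in, gives 79% in the first scenario but still 0% in the second (400 runs each, late arms on the same prior).

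Restricting P(best) to data from week six onward is optional. It would drop about 30 × 160 = 4,800 earlier children from the decision.

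The cost is protocol wording and a date switch in the code. The earliest stop moves to day 30 + 10 + 5 = 45, about week 9, so some children receive the weaker message for longer. That leaves about 20 of the 65 working days before the three-month limit.

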### Recruitment {15}

Community sensitisation is being led by the Ministry of Health and Ministry of Education. This includes TV and radio coverage explaining the Pono Yame screening programme. Our field coordinator will visit each region and work with schools to ensure that they are set up to enrol as many children as possible. Every referred child’s data will be included in the primary analysis. Subgroup analyses will only be permitted for children whose parents have consented for their sociodemographic data to be used for research purposes. This is a separate consenting process led by Peek.

### Assignment of interventions: allocation

#### Sequence generation, concealment and implementation {16a, 16b, 16c}

Participants will initially be randomly allocated into two arms using computer-generated blocks of 12. As allocation and intervention delivery (sending SMS messages) is fully automated, there is no need for any of the human investigators to know participant allocation status. Once the first participants attend refractive services, the algorithm will begin adjusting the allocation ratio to favour the best-performing arms. There is no need for the investigators to see allocation status at this stage either. The data safety monitoring committee will be fully unmasked to allocation status and all outcome data and will have the power to stop the trial or suspend any arm.

### Assignment of interventions: blinding

#### Who will be blinded {17a}

Trial participants will not be blinded. Programme implementers will check in participants when they attend clinic using Peek Capture. The software will automatically record the date and the time elapsed since referral. The adaptive algorithm will analyse attendance rates between arms according to pre-defined rules. Screening programme staff and data analysts will be blinded to assignment status. A small team of unblinded human statisticians will monitor the algorithm’s performance. They will double-check the algorithm’s working every 24 h during the trial and will repeat the final analysis comparing each arm. They will have the power to stop the trial, but they will not influence allocation.

#### Procedure for unblinding if needed {17b}

There is no procedure for unblinding.

### Data collection and management

#### Plans for assessment and collection of outcomes {18a}

Referral status, attendance status and days elapsed since referral will be collected using the Peek Capture system on Android devices. Every time a participant is referred and every time they attend at clinic, they are checked in using an android device operating Peek Capture software. Additional data on sociodemographic characteristics will be collected when participants initially present to the screening programme.

#### Plans to promote participant retention and complete follow-up {18b}

As the intervention is an SMS sent automatically by the programme, there is no scope for deviation. Similarly ‘loss to follow-up’ is the reciprocal for our primary outcome (attendance on appointed day).

#### Data management {19}

Data will be collected by Peek’s implementing partners using Android devices through the Peek Capture application. Peek Capture enforces security controls that include strong device passcodes and native Android encryption. Data stored is time limited, the device syncs via an encrypted connection with a Peek-managed server, the data is then deleted to minimise the risk of data stored on the device.

Data will be stored on a Peek-managed server hosted in a Virtual Private Cloud (VPC) utilising the Amazon Web Services (AWS) Cloud. Each Peek-powered programme is hosted on its own dedicated server and a VPC that will reside in the UK/EU ensuring all of the data privacy safeguards as governed under the GDPR. All data collected is securely stored in AWS data centres which are state of the art, utilising innovative architectural and engineering approaches. Routine manual data cleaning will be conducted periodically by Peek administrators. Internal software guardrails will pick up simple errors.

Data collected can be monitored using Peek Admin; it tracks the Programme progress, provides insights and helps ensure no one is left behind. Data exported from Peek Admin will be pseudo-anonymised removing names and any other key identifiers, only the least amount of data will be shared, and where possible it will be fully anonymised and aggregated for research purposes.

At the analysis stage, data will be sent via a secure file transfer, using an encrypted zip file to LSHTM researchers to perform statistical testing. The zip file will be saved on the protected LSHTM server and only authorised named project staff will be given access. Passwords will be sent separately. Further details can be found in the Data Management Plan (Additional file 1: Appendix 2).

#### Confidentiality {27}

Peek routinely collects sociodemographic information from each child who is referred on for refractive services including age, sex, location, ethnicity, religion, parents' occupation, parents' education, housing characteristics and asset ownership. This information will be held on a Peek-managed server hosted in a Virtual Private Cloud (VPC) utilising the Amazon Web Services (AWS) Cloud. Peek also seeks consent to use this data for research purposes.

Sociodemographic data on participants who have provided consent will be shared with the statistical analysis team at LSHTM for subgroup analysis. All team members who will access these data will have undertaken information security training. We will use encrypted data transfer and avoid cloud services outside the EU. The aggregated Peek data that is shared with LSHTM project staff will not contain any names; however, the data being shared may still permit the identification of individuals depending on the domains being shared and may therefore constitute pseudo-anonymised data. All data arising from this project will be stored securely for 10 years. Further information is provided in the data management plan (Additional file 1: Appendix 2).

#### Plans for collection, laboratory evaluation and storage of biological specimens for genetic or molecular analysis in this trial/future use {33}

Not applicable. We will not be using biological specimens.

### Statistical methods

#### Statistical methods for primary and secondary outcomes {20a}

This study will use Thompson sampling a Bayesian approach to identify the best arm. This is a Bayesian algorithm widely used to learn about arms and optimise decision making [27] Every 24 h, the probability of each arm being the best arm overall will be estimated, using Monte-Carlo simulations to get the posterior probability estimates. As there is no evidence available on how the messages would perform relative to another, a regularising prior of Beta(100,000) (i.e. centred at *p*=0.5 with a 90% credible interval of 0.44–0.56) will be used to avoid overfitting extreme data in the early phase of the trial. It is expected that about 1,000 children will enrol every day, and the observed data will begin to dominate the prior within the first couple of days. Each arm will have a probability of being best between 0 and 100%, and the sum of all two probabilities will equal 100%. These probabilities will be compared to the stopping rules as to whether the trial should stop or continue into the next day. If the trial is to continue, the proportion allocated to each arm for the next day will be updated to be proportional to the estimated probabilities. We will conduct all analyses using the runif and rbeta functions in R (R Foundation for Statistical Computing, Vienna, Austria). Figure 2 illustrates participant flow and operation of the algorithm.

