### Eligibility criteria {10}

Reminder messages will be sent to the registered mobile phone numbers of parents/guardians of children who test positive at screening and are referred on to clinic in the Pono Yame MoH/Peek Vision school screening programme in 2022. Provision of a mobile number is a pre-condition of entry into the screening programme, although parents/guardians are able to supply the number of a friend or relative so in practice this stipulation does not exclude any children.

Reminders will be sent in English and Setswana; spoken by >96% of the local population. The screening programme routinely collects data on preferred language, and reminders will be sent in the preferred tongue. Those who list any language other than English of Setswana will receive the reminder in both Setswana and English. The reminder will also be sent in both languages to those where data on language is not available for any reason. We will perform a secondary analysis that excludes these participants, but they will be included in the primary analysis.

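### The analysis section counts 1,000 screened children a day as enrolled when about 160 are randomised, misprints the prior, and at 160 a day the under-1% stopping rule is out of reach within three months

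*Protocol article*

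**What the plan says.** On daily numbers, the sample size section {14} states "Approximately 1000 children will be screened every day", and then "we expect approximately 160 of these children to be identified as requiring referral for further assessment and treatment". The eligibility section {10} sends messages only to parents or guardians of "children who test positive at screening and are referred on to clinic". The statistical methods section {20a} nevertheless says "about 1,000 children will enrol every day, and the observed data will begin to dominate the prior within the first couple of days".

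On the prior, the same section specifies "a regularising prior of Beta(100,000) (i.e. centred at *p*=0.5 with a 90% credible interval of 0.44–0.56".

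On stopping, sections {14} and {21b} give two rules, applied daily. The first is more than 95% probability that one arm is best. The second is "There is a >95% probability that the difference between the arms remaining in the study is <1" per cent. If neither is met, enrolment ends after three months of active screening. Section {14} adds that a conclusion might take anywhere from days to years.

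Other relevant facts: attendance is currently about 50% (background {6a}); the appointment is about a week after referral (outcomes {12}); the trial starts with two arms at 1:1, and the voice arms join after six weeks (trial design {8}).

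**The concern.** A child who is screened and not referred has no arm and no attendance outcome, so only the referred children inform the algorithm. The figure of 1,000 overstates that flow 6.25-fold (1,000 / 160), and the sentence about the prior rests on it.

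The printed prior has one number where a Beta distribution needs two, and it does not fit the interval beside it. Someone coding from the text needs to know which is meant.

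The wrong rate also hides a problem with the second rule. That rule is the only stated route to an early stop for no important difference. If it is out of reach at the true rate, the pair of rules is one-sided in practice, and a reader is misled about what the trial can conclude early.

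**Working it through.** **Inputs.** 160 randomised a day {14}; 50% attendance {6a}; two arms at 1:1 for the first six weeks {8}; outcome about 7 days after referral {12}; rule 2 margin 0.01 and threshold 0.95 {21b}. Assumed: three working months means 60 to 66 screening days, with 92 as an extreme.

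**1. The prior interval.** The plan's own figure is 0.44 to 0.56.
- Beta(100, 100): 5th and 95th percentiles 0.442 and 0.558. This reproduces it.
- Beta(100000, 100000): 0.498 and 0.502. This does not.

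The intended prior is therefore Beta(100, 100), with a weight of 100 + 100 = 200 children per arm.

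**2. When the data match the prior.**
- At 160 a day, two arms: 80 per arm per day, and 200 / 80 = 2.5 days of outcomes.
- At 1,000 a day, two arms: 500 per arm per day, and 200 / 500 = 0.4 days.
- Share of posterior weight from data after two days of outcomes: 160 / (160 + 200) = 0.44 at 160 a day, and 1,000 / (1,000 + 200) = 0.83 at 1,000 a day.
- Adding the lag at 160 a day: 7 + 2.5 = 9.5, so about day 9 to 10. In the first couple of days no appointment date has yet arrived.

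**3. Ceiling for rule 2.** Read the rule as P(|difference| < 0.01) > 0.95. The data most favourable to it are an observed difference of exactly zero with equal arms. With n per arm, attendance 0.5 and the prior included,

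SE = √(2 × 0.25 / (n + 201)), and P = 2Φ(0.01 / SE) − 1.

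| Screening days | n per arm at 160 a day | SE | P at 160 a day | P at 1,000 a day |
|---|---|---|---|---|
| 60 | 4,800 | 0.01000 | 0.68 | 0.986 |
| 63 | 5,040 | 0.00977 | 0.69 | 0.988 |
| 66 | 5,280 | 0.00955 | 0.70 | 0.990 |
| 92 | 7,360 | 0.00813 | 0.78 | 0.998 |

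These are upper limits, not expected values, and they count every outcome as already observed.

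**4. Departures from two equal arms, at 160 a day.**
- A 70:30 split over 60 to 66 days: 0.64 to 0.67.
- 30 days of two arms, then 33 days of four equal arms. Each SMS-only arm has 2,400 + 1,320 = 3,720 children and each voice arm 1,320. Pairwise P is about 0.62 (two SMS-only arms), 0.49 (SMS-only against voice) and 0.42 (two voice arms).
- In that design the probability that all four arms lie within 1 point is about 0.10.

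**5. What rule 2 would need.** P = 0.95 requires SE = 0.01 / 1.96 = 0.0051, so n + 201 = 0.5 / 0.0051², and n is about 19,007 per arm or 38,014 in total. That is 38,014 / 160 = 238 screening days, against 38,014 / 1,000 = 38 days at the mistaken rate with two arms.

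**6. Sensitivity to attendance.** At 80% attendance in both arms about 154 screening days are needed, and at 90% about 92.

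**The case against.** Several points on the other side stand.

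- The interval in the same sentence lets a careful reader recover Beta(100, 100). A reader might infer from the printed form that the trial will run on a prior its data could hardly move. The document does not support that, because such a prior contradicts its own interval.
- On rate alone the prior-dominance statement is only modestly wrong: 2.5 days of outcomes against a couple of days. The larger part of the gap is the one-week lag, which would apply at 1,000 a day as well. The allocation section {16a–c} already ties adaptation to the first attendances.
- If enrolling means entering the screening programme, the figure of 1,000 is right. The inference about the prior still fails, because unreferred children supply no outcome.
- A reader might conclude that rule 2 can never fire. That goes too far, because neither section defines the sign or the comparator of the difference. Under a one-sided reading (no other arm beats the leader by 1 point or more), the rule could be met at 63 days with an observed lead of about 0.6 points: 1.645 × 0.00977 − 0.01 = 0.0061. The text does not state that reading. Attendance near 90% would also make the rule borderline at 92 days.
- Section {14} concedes that a conclusion might take years, and {21b} says what happens if neither rule is met. The monitoring committee and the unblinded statisticians may also stop the trial. Failing to meet rule 2 therefore means running to the cap, not reaching a wrong decision.

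The caveat about years is general and depends on the effect. It does not tell the reader that rule 2 is out of reach under its plain reading even when the arms perform identically.

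**Conclusion.** The point holds as three linked corrections. The daily enrolment figure in {20a} contradicts {14} and {10} by a factor of 6.25. The printed prior does not match its own interval, which is that of Beta(100, 100). Rule 2, read as an absolute difference with attendance near 50%, cannot reach its 95% threshold within the cap: the ceiling is about 0.68 to 0.70 at 60 to 66 screening days and 0.78 at 92, and lower under unequal allocation or once the voice arms join. An early stop by a stated rule is thus in practice possible only for a winner.

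The conclusion on rule 2 rests on the assumed number of screening days, on attendance well below 90%, and on the two-sided reading. It does not follow that the trial's final comparison is invalid or that a sample size is wrong: the algorithm works on actual accrual, and no sample size was derived from the 1,000.

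**What to change.** In {20a}:
- state about 160 randomised children a day;
- print the prior as Beta(100, 100) for each arm, and confirm that the code uses it;
- say that with two arms the data match the prior's weight at about day 9 to 10, including the week until the appointment.

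In {14} and {21b}:
- define the difference (absolute or relative, two-sided or one-sided, and between which arms when more than two remain);
- then either state that rule 2 is not expected to be met within three months, or have the sponsor reset its margin from simulations that use the actual accrual, the outcome lag, the adaptive allocation and the staggered arms. The documents give no basis for a particular alternative margin, so that choice is the sponsor's.

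The cost is a text correction and one code check, plus a simulation exercise if the margin is reset. The stated speed of learning and the ability to stop for no important difference will look less favourable.
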